**Intestinal Barrier Function Changes in Response to Administration of Corticotropin Releasing Hormone and High Fat Diet**

**Background**

| The last decade has seen a number of studies supporting the theory of chronic intestinal barrier perturbation in the pathogenesis of IBD and many other human diseases.^1–4^ Stress – a state which evokes a ‘fight or flight’ or sympathetic response from the human organism - has been implicated in the propagation of inflammation in patients with inflammatory bowel disease (IBD). Indeed, the risk of relapse in both Crohns disease (CD) and Ulcerative colitis (UC) increases in the presence of both acute and chronic stress. ^5–7^ The mechanism proposed for this phenomenon includes the ability of stress to induce a breakdown in intestinal barrier function via mast cell- and corticotropin releasing hormone (CRH)-dependent pathways. ^8^ This intestinal barrier perturbation has been demonstrated experimentally in humans using stress paradigms which could be equated to the relatively mild stressful events experienced in every-day life, such as public speaking.^9–11^, although replicating this has practical difficulties in a research setting. Another established way to induce intestinal stress is through diet.  The autonomic nervous system (ANS) appears to be playing a crucial role in stress-induced changes in intestinal permeability. Multiple in vitro and in vivo murine model studies have confirmed that both acute and chronic stress (induced in a mouse by various stress paradigms such as restraint and water emersion) can promote increased intestinal permeability. The underlying mechanism seems to be via the disruption of tight junction proteins along the paracellular space of the intestinal epithelium.^15,16^ The disruption of tight junctions in these stress paradigm models are dependent on acetylcholine and CRH. ^11,17^ This effect on intestinal permeability appears to recover within 4 days in murine models.^18^ Similar changes have been described in human models of acute stress. Changes in intestinal permeability induced by acute stress can be mimicked by peripheral administration of CRH.^19^  Corticotropin releasing hormone (CRH) is naturally secreted from the healthy human hypothalamus during periods of stress. Intravenously administered CRH possesses the advantage of having a short half-life and is routinely clinically utilised in the diagnosis of Cushing’s syndrome.^12,13^ Recent evidence has shown that injecting CRH intravenously reliably and significantly increases intestinal permeability in healthy volunteers with no significant adverse effects.(12) The timeline of this increase, and its effect on the serum intestinal permeability measurements have not been established.  Food-induced stress has also shown to temporarily impair barrier function in healthy subjects with a standardised ‘high fat high carbohydrate’ meal. This challenge meal, comprising 50-60 g fat and 80 g carbohydrate, caused bacterial translocation indicated by increased sCD14 and LBP^14^, although it is not known if these changes are maintained beyond four hours. This standardised meal has been used in research setting in many studies and is accepted as gold standard. However, using food as a model to represent IBD has its limitations. Food is complex in its composition and has many confounding nutrient factors, background diet is rarely considered and may impact outcomes, blinding is difficult, recruitment of study participants will automatically exclude those with dietary restrictions or certain food dislikes and using food-induced stress is not appropriate for trials investigating dietary therapies. Furthermore, it is difficult to translate the findings into real world, which involves constant ingestion of food. We need a more reliable model of experimentally inducing intestinal barrier dysfunction in humans.  Several serological and urinary markers have been validated as useful tools in measuring intestinal  permeability changes in vivo. These include lipopolysaccharide-binding protein (LBP), soluble CD-14  (sCD14), syndecan-1 and intestinal-type fatty acid-binding protein (I-FABP) in the serum. Because  sCD-14 and LBP are part of the LPS inflammatory signalling pathway, their levels in serum are believed  to be objective markers for systemic immune activation and damage to gut epithelium.^14,20^.  I-FABP is an intracellular protein expressed in the epithelial cells of the mucosal layer of the small  and large intestine tissue and is prone to leakage into the blood stream from the enterocytes when  intestinal mucosal damage occurs.^21^ Syndecan-1 is a key component of the glycocalyx layer of the  intestinal endothelial surface.^21^ Syndecan-1 is crucial to the maintenance of the intestinal epithelial  barrier function^22^ and its release into the circulation indicates perturbation of the intestinal barrier.^23,24^  While I-FABP and syndecan-1 are preformed and would be rapidly released on intestinal injury in association with acute stress, such as a single meal (as above) or CRH administration, the validity of the serum/plasma markers, LPB and sCD14, requires critical examination. The response of these markers is dependent upon new protein synthesis in response to cytokine release (specifically IL-1, IL-6 and TNFα) related to increased LPS/endotoxin exposure following changes in barrier function. Since such production is transcriptionally regulated, there will be a delay in detecting a rise in the concentrations of LPB and sCD14. In rabbits stimulated with silver nitrate, transcription had a delay of up to 2 hours. Subsequent LBP levels in serum were elevated at 4 hours after the stimulus and were maximal at 24 hours.^25^ The studies examining LPB and sCD14 after a high fat meal had changes observed within the first 2 hours.^14^ This is not easy to reconcile with new induction of protein synthesis and might reflect washing out of hose proteins from the intestinal mucosa via increased lymphatic flow, as previously shown for hyaluronic acid.^26^ Whatever the case, the question of the time course of events requires clarification.  We aim to develop a model of intestinal permeability perturbation in healthy human volunteers with both CRH and a standardised high fat high carbohydrate meal. This will allow for future studies to experimentally test therapeutic efficacy of CRH on the intestinal barrier function.  **AIMS:**   1. To develop models of intestinal permeability perturbation in healthy human volunteers utilising 2 strategies  - Physiological stress induction by intravenous CRH injection - Clarification and further exploration of the stress effect of a standardised high-fat high-carbohydrate (HFHC) meal on intestinal barrier dysfunction. This data will be used in future studies to dissect out the particular dietary components within this meal which specifically induce permeability changes.  1. To characterise the models in terms of optimal timing of blood sampling circulating markers of intestinal barrier dysfunction   **HYPOTHESES:**   1. Both CRH and the high-fat high-carbohydrate meal will increase intestinal permeability over a normal saline injection as measured by serum markers of intestinal permeability (I-FABP, Syndecan-1, CD14 and LBP). 2. There are differences in optimal timing of the measurement of circulating markers.     **Project Design**  This will be a single centre, randomised, placebo-controlled cross-over study to investigate the effect of CRH and a HFHC meal on intestinal permeability. (See ***Figure 1***).  ***Figure 1***  ***[figure not shown]***  **Inclusion criteria:**   - Healthy males and females between the ages of 18 – 65 - Participants who are able to give informed consent - Volunteers should be able to attend Monash University, Alfred Campus on 7 occasions   **Exclusion Criteria**   - Inclusion criteria not met - Past medical history of diabetes (type 1 or 2) - Past medical history of inflammatory bowel disease, coeliac disease, a diagnosis of irritable bowel syndrome or significant gastrointestinal symptoms not otherwise medically diagnosed - Patients actively taking non-steroidal anti-inflammatory medications (NSAIDs) or corticosteroids - Probiotic or antibiotic intake over the past 2 months - Pregnant or breast feeding participants - Allergy or intolerance to the components of the proposed meals   **Recruitment process**  Participants will be recruited using advertising posters and word of mouth from the Monash University community.  **Study Procedures**  These are explained in ***Figure 2*** and in further detail below  ***Figure 2***  **Visit 1 and 2**   \| **Time (minutes)** \| **T = -30** \| **T = 0** \| **T = 2 hours** \| **T = 6 hours** \| **T = 24 hours** \| \| --- \| --- \| --- \| --- \| --- \| --- \| \| **Intervention** \| - Cannula insertion and initial blood sample \| - CRH or placebo injection - Further blood sample \| - Blood sample \| - Blood sample - Cannula removal \| - Blood sample   **END OF VISIT 1 AND 2** \|   **Visit 3 and 4**   \| **Time (minutes)** \| **T = -30** \| **T = 0** \| **T = 2 hours** \| **T = 6 hours** \| **T = 24 hours** \| \| --- \| --- \| --- \| --- \| --- \| --- \| \| **Intervention** \| - Cannula insertion and initial blood sample \| - High fat , high carbohydrate meal to participant - Further blood sample \| - Blood sample \| - Blood sample - Cannula removal \| - Blood sample   **END OF VISIT 3 AND 4** \|   *Participants will be asked to obtain from alcohol and intense exercise for 3 days prior to each of the study visits.*  **Screening visit**  Participants will be invited to meet with the study staff in order to ensure eligibility and seek informed consent. They will be informed whether or not they meet inclusion criteria at the end of the screening visit. They will be given a list of foods which are low in fat and carbohydrates. These are the only foods that they will be able to consume for the duration of the visits.  *All blood tests will involve 2x 10ml blood test tubes drown from the participants’ vein unless otherwise stated*  **Visit 1**   - Participants will, if they wish, have a light breakfast consisting of foods from a prespecified list which have a low fat and low carbohydrate content. - On presentation to the department, participants will be randomised to receive either a CRH or placebo injection. - They will then have a cannula inserted and have blood drawn. This will be the Time (T) = -30 minute blood test. - Participants will have a further blood test at the T=0 mark and then have either CRH or placebo injected into their cannula. - They will have further blood tests at the T=2 and T= 6 hour marks. - Participants will be asked to remain near the department for the duration of the study visit and will be offered a light hearted video to watch for the period of their visit. - After T=6 hours, the cannula will be removed and participants will be free to leave the department. - A low fat, low carbohydrate late lunch meal will be provided to the participants on completion of   this visit and instructions for how to prepare a low fat, low carbohydrate dinner will be given to them to follow for their evening meal.  **Visit 2**   - Participants will be asked to return the day after Visit 1 – at T = 24 hours post the initial CRH or placebo injection in order to have their final blood tests.   ***Visits 1 and 2 will be replicated during visits 3 and 4 with the alternative intervention.***  **Visit 5**   - Participants will be asked to present to Monash University, The Alfred Hospital campus. - They will have a cannula inserted and have blood taken. This will be the T = -30 sample - They will then receive the high fat meal. - ***Participants will not be informed of the nature of the meal that they are receiving*** - They will eat the meal and have the second blood test immediately after they have finished eating. This will be the T = 0 blood test. - They will have further blood tests at T = 2 and T = 6 hour mark, after which time they will have their cannula removed and they will be free to leave the department. - A low fat, low carbohydrate late lunch meal will again be provided to the participants on completion of this visit and instructions for how to prepare a low fat, low carbohydrate dinner will be given to them to follow for their evening meal.   **Visit 6**   - The participant will be asked to return at the 24 hour mark where they will have a further blood test performed.   **Outcome measures**  ***Primary outcome measures:***  Change in intestinal permeability over the different time points in response to CRH, placebo and meal challenge as measure by:   - - Serum I-FABP, Serum CD14, serum syndecan-1 and Serum LBP as measured by the ELISA   **Data Collection/Gathering**  After obtaining informed consent, data will be collected on the participants’ demographics. This will be stored in a secure, password protected database in a re-identifiable fashion. Paper records will be kept on site at Monash university in a secure location.  **Participant Safety and Withdrawal**  ***Risk management and safety***  ***The potential for intravenous CRH administration to cause side effects***  CRH is a hormone naturally produced in the human hypothalamus in response to stress. Its intravenous preparation is used routinely in clinical practice for the diagnosis of Cushings syndrome at a dose of 200 μg.^13^ CRH has rarely been associated with side effects such as flushing and tachycardia when administered at doses ***greater*** than 200 μg and its pharmacology has been thoroughly characterised in multiple previous studies.^13,16^ We are proposing to administer 100 μg, which is half of that used in routine clinical practice. Multiple studies have been performed on healthy human volunteers and higher at this dose of CRH with no reported side effects aside from *some minor facial flushing* in one study 30 minutes post administration.^13,15,19^ Participants will be monitored in the presence of medical staff throughout this period.  ***The standardised challenge meal***  The standardised meal will provide 56-60 g total fat, 82 g carbohydrate and 28-30 g protein and will consist of two sausage, egg and cheese sandwiches with two hash browns. This challenge meal has been used in similar studies.  ***Pain/discomfort/distress during interventions, particularly cannulation for CRH administration and blood taking***  Participants will all undergo informed consent where a member of the investigator team will be able to guide them through the interventions. They will be reassured and informed that they can stop being involved in the study at any point of their choosing. Cannulation, blood taking and CRH administration will be performed by an experienced medical practitioner. The cannula will remain in-situ for no longer than the duration of the visit (6.5 hours). This is well below the recommended 72 hours (or 3 days) of cannulation duration in Australian hospitals.  ***Withdrawals***  Participants are able to withdraw from the study at any point in time. The data will be collected up until the withdrawal from the study and included in the final analysis.  ***Replacements***  If a participant chooses to withdraw from the study prior to completion a further patient will be recruited until a total of 10 patients have completed the study.  **Storage of blood and data security**  ***Blood and Tissue Storage***  Two vials of serum will be stored in aliquots for further analysis. These samples will be assigned to the participant’s research code and will remain within the Monash University at the Alfred Hospital. After analysis has been completed the blood and tissue will be destroyed.  ***Data Security***  Electronic records of participant data will be kept securely with the principal investigator whilst paper records will be kept at Monash university. At the completion of the study all records will be kept with the principal investigator for at least 7 years. All electronic records will require password access and paper records will be in security tag accessible areas within locked storage units.  **Data Analysis**  Given that this is the first study investigating the timeline of intestinal permeability change in response to the described stimuli, a sample size of 10 participants has been chosen to initially explore these effects. The median values of the quantitative results of the ELISA will be compared between the 3 different conditions. Non parametric paired analyses will be performed and a statistical criterion of p<0.05 as significant will be adopted. | |
| --- | --- | --- | --- | --- | --- | --- | --- | --- | --- | --- | --- | --- | --- | --- | --- | --- | --- | --- | --- | --- | --- | --- | --- | --- | --- |
|  |  |

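### Only CRH versus saline is randomised; everyone gets the meal afterwards, so the meal-versus-saline half of Hypothesis 1 cannot be separated from period

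*Protocol*

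**What the plan says.** The Project Design statement covers both interventions with one label: "This will be a single centre, randomised, placebo-controlled cross-over study to investigate the effect of CRH and a HFHC meal on intestinal permeability". Hypothesis 1 then sets both against the same control: "Both CRH and the high-fat high-carbohydrate meal will increase intestinal permeability over a normal saline injection". Data Analysis compares marker medians across the three conditions by paired non-parametric tests at p<0.05, and does not distinguish one contrast from another.

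The only allocation step is in the Visit 1 text, where "participants will be randomised to receive either a CRH or placebo injection". The second session completes a two-period cross-over of the injections: "Visits 1 and 2 will be replicated during visits 3 and 4 with the alternative intervention". At Visit 5 there is no allocation and no control meal. Blood is taken and, for everyone, "They will then receive the high fat meal".

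The inclusion criteria fit this order: "Volunteers should be able to attend Monash University, Alfred Campus on 7 occasions" matches a screening visit plus Visits 1 to 6. The second table in Figure 2 disagrees, because it places the meal at Visits 3 and 4. The table and the visit text must be reconciled, but under either one the meal follows an injection session.

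**The concern.** In a randomised cross-over, shuffling the order of conditions keeps anything that changes between sessions from being mistaken for a treatment effect. Here the injections are shuffled and the meal is not. Saline falls in period 1 or 2, and the meal always falls in period 3. By then every participant has had CRH, saline and two earlier cannulated sampling days, whereas saline is preceded by nothing or by CRH alone.

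Period effects are plausible, though not shown. The Background attributes barrier changes to stress of an everyday kind, and the safety section lists distress from cannulation as a risk. The visible text states no interval between sessions, and the only recovery time it gives is 4 days, in mice.

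Half of Hypothesis 1 would thus be tested on a non-randomised contrast under a randomised, placebo-controlled label. The protocol also intends the meal data to guide later work on individual dietary components, so a period artefact, or a real effect masked by one, could carry forward.

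**Working it through.** **No figure to reproduce.** The sample size of 10 is described as exploratory and has no effect size, SD or power behind it. The check is therefore whether the contrast can be estimated at all.

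**1. Estimability.** Inputs: 10 completers (Replacements; Data Analysis) and the sequences CRH-saline-meal and saline-CRH-meal (visit text), assumed to be split 5 and 5. The model is response = subject + period + treatment + error.

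- Columns: 10 subject + 2 period + 2 treatment = 14.
- The meal column is 1 exactly where the period-3 column is 1, so the two are identical and the rank is 14 - 1 = 13.
- CRH minus saline is estimable, with variance 0.20σ², where σ is the within-subject SD.
- Meal minus saline is not estimable, with or without a first-order carryover term.
- If all six orders are used, the rank is full: 14 of 14 with 10 participants (unbalanced) and 16 of 16 with 12 (balanced).

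**2. What the baseline sample removes.** Write the session-p value at time t as level_p + response_p(t). Change from T=-30 cancels level_p. It does not cancel a difference between sessions in response_p(t), such as a reaction to cannulation that fades with experience.

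**3. Bias under an assumed drift.** Let the response drift linearly by δ from period 1 to period 3, so that the shifts are 0, δ/2 and δ.

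- Mean shift for saline: (0 + δ/2)/2 = δ/4.
- Shift for the meal: δ.
- Bias in meal minus saline: δ - δ/4 = 3δ/4.

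**4. Effect on the planned test.** Exact signed-rank test, n=10, two-sided 0.05 (the protocol does not state sidedness), normal errors, no true meal effect, 200,000 simulated trials:

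| Drift δ (within-subject SD) | Bias, 3δ/4 (SD) | Rejections |
| --- | --- | --- |
| 0 | 0 | about 5% |
| 0.5 | 0.375 | about 11% |
| 1.0 | 0.75 | about 30% |
| 1.5 | 1.125 | about 56% |

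A negative drift of the same size gives the same totals, but almost all of those rejections say that the meal is lower than saline. At δ = -0.5, wrong results favouring the meal fall to about 0.3%. The documents give no drift size, so these rows are illustrations only.

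**The case against.** The strongest reply is that this is a first, exploratory study of 10 people, that the visit text openly shows which step is randomised, and that the primary outcome is a change over time with a pre-exposure sample in every session. Much of that stands, and it rules out several stronger readings.

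- **A reader might infer that any calendar or seasonal drift passes straight into the meal result.** It does not if change from T=-30 is analysed, because a stable difference in level cancels. Only a difference in response between sessions survives. Data Analysis speaks loosely of medians, so the use of change should be stated.
- **A reader might infer that all carryover is aliased with the meal.** The injection immediately before the meal differs by randomised sequence, so a simple first-order CRH carryover term is not fully aliased. Period and cumulative exposure are.
- **A reader might infer that the design favours Hypothesis 1.** The mechanism closest to the text, habituation to cannulation, would raise saline-session responses relative to the meal session and so hide a meal effect. Other drift could mimic one. The documents do not settle the direction.
- **A reader might infer that the whole trial is compromised.** CRH versus saline is randomised and unaffected.

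Figure 1 is not shown and might depict the order or a washout, but the visit text is explicit. The exploratory aim lowers the stakes. It does not make the design label true for the meal, and a statistical analysis plan cannot recover a contrast that the design does not identify.

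**Conclusion.** The point holds. Meal minus saline is exactly aliased with period and with cumulative prior exposure. That conclusion rests only on the meal coming last for everyone, which is true under both the visit text and the Figure 2 table. The size and sign of any resulting bias are unknown. The 11%, 30% and 56% error rates depend on assumed linear drifts in response, an equal split of sequences, normal errors and a two-sided test. Given the exploratory aim and the intact CRH-saline comparison, this should be fixed, but it does not undermine the trial as a whole.

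**What to change.** **Minimum change, wording only.** State in Project Design that only CRH versus saline is randomised and placebo-controlled. Analyse the meal as within-session change from its own T=-30 sample. Report meal versus saline as a non-randomised, exploratory comparison confounded with period, and reword Hypothesis 1 to match. Reconcile the Figure 2 table with the Visit 3 to 6 text. This needs no change to visits, samples or participants. The price is a weaker claim for the meal.

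**Alternative, only possible before enrolment.** Randomise the order of all three conditions and include period in the analysis. With 10 participants meal minus saline becomes estimable (variance about 0.21σ²), and CRH minus saline keeps its 0.20σ², with no extra visits or participants. There are three costs:

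- In four of the six orders the meal would directly precede an injection session. That exposes the CRH-saline contrast to meal carryover from which it is now free, so the protocol would have to state a washout between sessions.
- The simple paired tests would have to give way to a period-adjusted analysis.
- Six orders do not divide evenly into 10 participants, although the contrast remains estimable.

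Even then, a saline injection is not a placebo for a meal, so the placebo-controlled label should stay with the CRH comparison.

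### Food intake before and during sessions is not fixed alike: breakfast is optional on both injection days and Visit 5 has no rule, so fed state may differ between paired sessions

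*Protocol*

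**What the plan says.** All references are to the protocol.

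- **Visit 1 (CRH or placebo):** "Participants will, if they wish, have a light breakfast consisting of foods from a prespecified list"; the listed foods are low in fat and carbohydrate. No time, amount or minimum interval before the T = -30 sample is given.
- **Visit 3 (the other injection):** "Visits 1 and 2 will be replicated during visits 3 and 4 with the alternative intervention". The option carries over; nothing asks the participant to repeat the earlier choice.
- **Visit 5 (challenge meal):** the text goes from arrival straight to "They will have a cannula inserted and have blood taken. This will be the T = -30 sample" and then to the meal. It mentions neither breakfast nor fasting.
- **Screening visit:** participants receive a list of low-fat, low-carbohydrate foods, and "These are the only foods that they will be able to consume for the duration of the visits". This limits what may be eaten, not whether, when or how much.
- **Background:** markers moved within 2 hours of a high-fat meal, which for LBP and sCD14 "might reflect washing out of hose proteins from the intestinal mucosa via increased lymphatic flow". Among the limits of food models it lists that "background diet is rarely considered and may impact outcomes".
- **Data Analysis:** the three conditions are compared by non-parametric paired tests at p<0.05, with 10 participants.

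**The concern.** The design rests on each participant being their own control. That works only if the sessions differ in the intervention and otherwise as little as possible. As written, a participant may eat before one injection session and not before the other, and may arrive at Visit 5 in either state.

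The protocol treats food as potentially active on these endpoints. Besides the wash-out remark, it says that I-FABP and syndecan-1 "would be rapidly released on intestinal injury in association with acute stress, such as a single meal (as above) or CRH administration". Hypothesis 1 compares the meal with a saline injection, so the comparator for a meal is a day on which intake is left to the participant. The second aim is the timing of marker changes, and an untimed breakfast could blur exactly that. The Data Collection section mentions demographics only, so no intake record is provided for that would let the analyst sort this out afterwards.

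**Working it through.** **1. The three sessions side by side**

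| Session | Intake before T = -30 | Intake from T = -30 to T = 6 h |
|---|---|---|
| Visit 1 (CRH or saline) | Optional, listed foods, untimed | Listed foods only; lunch after T = 6 |
| Visit 3 (the other injection) | Same option, choice need not be repeated | As Visit 1 |
| Visit 5 (meal) | No rule stated | Challenge meal; otherwise listed foods only; lunch after T = 6 |

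No sentence makes the first column the same for the three sessions.

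**2. Noise or bias**

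- *CRH versus saline.* The same optional rule applies on both days and the injection order is randomised. An unequal choice adds variance and shifts nothing on average.
- *Meal versus saline.* Visit 5 is always last and has no breakfast rule. If breakfast is commoner on saline days than at Visit 5, or the reverse, the difference is systematic. Its sign depends on which session is fed more often and on whether breakfast raises the post-baseline values or the baseline. The protocol settles neither.

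**3. Illustration of size**

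The protocol gives no effect size, SD or power for its 10 participants, so there is no stated figure to reproduce. All of the following are assumptions: paired differences are normal with SD 1; breakfast shifts the marker upward by d (in SDs of the paired difference); half of participants eat it on any injection day, chosen independently; nobody eats it at Visit 5; the true effect is 0.8 SD. The test is the two-sided signed-rank test with n = 10, rejecting when the smaller rank sum is 8 or less.

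CRH–saline: the mean stays at 0.8 and the variance becomes 1 + d²(0.25 + 0.25) = 1 + d²/2, that is 1.02, 1.125 or 1.5 for d = 0.2, 0.5 or 1.

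Meal–saline: the mean becomes 0.8 − d/2, that is 0.70, 0.55 or 0.30, and the variance 1 + d²/4, that is 1.01, 1.0625 or 1.25.

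Simulated power (200,000 runs per cell):

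| d | CRH–saline | Meal–saline |
|---|---|---|
| 0 | 0.60 | 0.60 |
| 0.2 | 0.59 | about 0.48 |
| 0.5 | 0.55 | 0.31 |
| 1 | 0.43 | 0.11 |

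Separate simulations put the d = 0.2 meal–saline value at 0.48 to 0.49; the others agree to within about 0.01.

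**4. Direction of false rejections**

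With no true effect, the meal–saline test rejects in about 10% of trials at d = 0.5 and 23% at d = 1, against a nominal 5%. Split by direction, nearly all of these say that the meal is *below* saline: about 0.098 of 0.102 at d = 0.5, and 0.232 with under 0.001 the other way at d = 1. If breakfast instead lowers the measured change, for example by raising the baseline, the same figures apply with the sign reversed.

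**The case against.** The case for leaving the text alone has real force.

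- **Breakfast may not matter.** The Background statements concern a high-fat challenge meal, and the wash-out explanation is hedged. Nothing there says that a light low-fat, low-carbohydrate breakfast moves any marker. This stands: an effect is plausible, but its size is unknown and could be nil.
- **Choices may be consistent.** Fed state may differ; the text does not show that it does. If everyone repeats the same choice, CRH–saline loses nothing. If 80% always repeat it and the rest choose independently, power is 0.588 at d = 0.5 and 0.558 at d = 1. This also stands.
- **Controls already exist.** All intake is limited to one list, lunch comes after T = 6, and the T = -30 and T = 0 samples allow change from baseline. That removes a constant offset, but not a response to breakfast still evolving during the session. At Visit 5 the T = 0 sample follows the meal, so only T = -30 precedes it.
- **The study is exploratory.** True, but it is meant to fix sampling times and inform later studies, and 10 participants leave little room for avoidable within-person variation.

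Two stronger readings are tempting. A reader might infer that the breakfast rule will produce a spurious rise after the meal. The documents give no direction, and if breakfast raises the markers on saline days the bias runs the other way and hides a real meal effect. A reader might also infer that an early LBP or sCD14 rise could be due to eating as such because breakfast is optional. That ambiguity comes from having an injection, and no control meal, as comparator; a breakfast rule would not remove it.

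**Conclusion.** The point holds as a gap in standardisation. Intake before baseline is optional on two of the three paired sessions, unstated on the third, and not required to match. This is clear from the text. It adds noise to CRH versus saline and can bias meal versus saline in either direction.

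The consequence is much less certain than the gap. The illustrated loss runs from negligible (CRH–saline power 0.60 to 0.59 at d = 0.2) to severe (meal–saline power 0.60 to 0.11 at d = 1). It rests on an assumed upward shift and on assumed 50% independent uptake with none at Visit 5, none of which the protocol gives. With a shift of zero there is no effect on either comparison. The change is worth making because it is cheap and the paired design depends on comparable sessions; a serious loss has not been demonstrated.

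**What to change.** 1. In Visit 1 (and so Visit 3), replace the optional breakfast with one stated pre-visit intake rule, and put the identical rule in Visit 5. Which rule to adopt is for the investigators; what matters here is that it is the same for every participant and all three sessions.
2. State one identical rule for intake between T = -30 and T = 6 hours in all three sessions, apart from the challenge meal itself.
3. Record at each session what was eaten and when, so that departures can be seen in the analysis.
4. Separately, because the comparator is a saline injection, describe that contrast as *HFHC meal versus no challenge meal*.

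The cost is revised wording, participant instructions and a short intake record, with slightly more burden on participants. No visit, sample or assay is added.
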